### 2.5 Data collection and analysis

Behavioral data will be collected at multiple time points to evaluate the impact of tACS on food cravings and inhibitory control. The S-FCQ, FCI, and Go/No-Go task will be administered pre- and post-stimulation on Days 1 and 5, and again on Day 8 to assess short-term changes in craving and impulse regulation (Figure 1). Broader trait-level assessments, including the YFAS 2.0 and the T-FCQ, will be administered at baseline (Day 0) and again during the follow-up session on Day 15 to examine long-term or sustained effects (Figure 1).

Electroencephalographic data will be recorded on Days 1, 5, and 7 (Figure 1) using a 64-channel dry electrode cap following the international 10–20 system. Each EEG session will include 5 min of resting-state recording with eyes open, followed by 5 min of viewing food-related and neutral images. Recordings will be conducted both before and after stimulation to detect aftereffects. EEG data will be acquired using the ANT Neuro system at a sampling rate of 1064 Hz. Impedance will be maintained below 10 kΩ. Signal preprocessing and artifact correction will be performed using standard pipelines in EEGLAB and custom MATLAB scripts. Key neural indices will include spectral power, PLV, and ERPs.

Functional MRI data will be acquired using a Siemens 3T Prisma scanner with a 64-channel head coil. Imaging sessions will occur at baseline (Day 0), immediately post-tACS on Day 2, and again post-intervention (Day 8) (Figure 1). Each session will include an 8-min resting-state scan and a cue-reactivity task involving the passive viewing of highly palatable food and neutral images. The cue task will use a block design format with craving intensity ratings collected after each block. BOLD signal changes will be analyzed using Statistical Parametric Mapping 12 (SPM12) and FMRIB Software Library (FSL), with preprocessing steps including realignment, normalization, and spatial smoothing. Functional connectivity will be assessed using seed-based correlation and ICA approaches, focusing on DLPFC, ACC, and insula as predefined regions of interest.

All adverse events or discomforts related to tACS will be monitored daily throughout the intervention phase. Any participant experiencing persistent adverse effects will be withdrawn from the study and referred for appropriate follow-up care.

Data management will be conducted in accordance with ethical data protection standards. All data will be stored on a secure, encrypted server with access limited to authorized personnel. Personal identifiers will be removed and replaced with anonymized participant codes. Missing data will be handled using multiple imputations via chained equations (MICE), assuming data are missing at random. Sensitivity analyses will be conducted to test the robustness of findings under different imputation models.

All statistical analyses will follow an intention-to-treat approach. The primary outcome–change in S-FCQ and FCI scores–will be analyzed using repeated measures ANOVA, with time (pre/post) and group (stimulation target and sham) as factors. *Post hoc* comparisons will be corrected using the Bonferroni method. Changes in Go/No-Go performance will be analyzed using ANCOVA, adjusting baseline reaction times and error rates. EEG parameters will be analyzed using linear mixed-effects models to account for within-subject correlations across sessions. Functional connectivity changes in fMRI will be assessed using seed-based and ICA models, with between-group comparisons conducted using *t*-tests or mixed models where appropriate. Longitudinal changes in YFAS and T-FCQ scores will be modeled using hierarchical linear regression.

Exploratory analyses will examine whether individual differences in sex, BMI, and baseline craving severity moderate the effects of tACS. Clustering methods will also be used to identify subgroups based on EEG and fMRI response profiles.

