### 2.4 Outcome measures

The primary outcomes of this study are changes in food craving intensity and inhibitory control following the tACS intervention. Craving will be assessed using the State Food Craving Questionnaire (S-FCQ) and the Food Craving Inventory (FCI), both administered before and immediately after stimulation sessions on Days 1 and 5 (Figure 1). Inhibitory control will be evaluated using a computerized Go/No-Go task at the same time points. These behavioral measures will provide insight into the acute and cumulative effects of tACS on craving regulation and impulse control.

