**FIGURE 1 F1:**
[figure not shown]
Overview of the study timeline, including screening, intervention, and follow-up phases. This schematic illustrates the flow of participant activities and data collection across all phases of the study. Screening and baseline evaluations (Day 0) include eligibility verification, informed consent, structural MRI, and administration of behavioral questionnaires (YFAS 2.0, T-FCQ, CESD-R). The intervention phase (Days 1–7) involves daily tACS, with EEG performed on Days 1, 5, and 7, and behavioral assessments (S-FCQ, FCI, Go/No-Go task) performed on Days 1, 5, and 8. An fMRI will be performed post-tACS on Day 2. Post-intervention imaging (fMRI) and follow-up behavioral measures occur on Day 8. A follow-up assessment on Day 15 evaluates potential sustained effects and adverse events.

Secondary outcomes will focus on neural mechanisms underlying these behavioral changes. EEG will be recorded immediately before and after stimulation on Days 1, 5, and 7 to capture neurophysiological aftereffects (Figure 1). Key EEG parameters include frequency-specific power changes indicative of entrainment, phase-locking value (PLV), and event-related potentials (ERPs). Data will be analyzed at both sensor and source levels using established pipelines.

Functional magnetic resonance imaging will be used to assess changes in functional connectivity within craving-related neural networks. Imaging will be conducted pre- and post-intervention (Day 0 and Day 8) and will include both resting-state scans and a cue-reactivity paradigm (Figure 1). Connectivity will be examined using seed-based correlation and independent component analysis (ICA), targeting the impulsive (ACC), reflective (DLPFC), and interoceptive (insula) systems, which correspond to the stimulation targets.

Craving-related traits will be assessed using the T-FCQ and the YFAS 2.0, administered at baseline (Day 0), and again during follow-up (Day 15) (Figure 1). These measures will provide a broader understanding of individual differences in craving susceptibility and their potential modulation by tACS.

Finally, follow-up assessments on Day 15 will evaluate whether observed behavioral and neural changes persist beyond the immediate intervention phase. This longitudinal component is designed to assess the sustainability of tACS effects and explore delayed neuroplastic adaptations.

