## 4 Ethics and dissemination

This study will be conducted in accordance with the ethical principles outlined in the Declaration of Helsinki and complies with international guidelines for human subject research. Ethical approval has been sought from both the Abu Dhabi Health Research and Technology Committee (ADHRTC) and the Human Research Ethics Committee of the United Arab Emirates University (UAEU-HREC). Final approval will be obtained prior to initiating participant enrollment.

All participants will provide written informed consent prior to participation. During the consent process, participants will be informed of the study’s objectives, procedures, potential risks and benefits, confidentiality safeguards, and their right to withdraw at any time without penalty or loss of entitlements. Consent will be obtained in a private setting and documented electronically and in writing.

To ensure participant safety, rigorous exclusion criteria have been implemented to minimize risks associated with tACS and MRI procedures. Adverse events will be closely monitored throughout the study, and any serious or unexpected effects will be reported to the ethics committees in accordance with regulatory standards. Participants experiencing adverse effects will be offered appropriate support and may be withdrawn from the study if necessary.

Confidentiality will be maintained by assigning a unique study ID to each participant. All identifiable data will be securely stored and accessible only to authorized members of the research team. De-identified data will be used for analysis, publication, and data sharing. Data handling and storage procedures will comply with institutional and national data protection regulations.

Any protocol amendments, including changes to eligibility, intervention procedures, or outcome assessments, will be submitted for ethics committee approval and documented in trial records. The study will be registered in a publicly accessible clinical trial registry before participant enrollment, and findings will be disseminated through peer-reviewed publications and conference presentations in accordance with open science principles.

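### Persistent adverse effects lead to withdrawal from the study, not only from stimulation, so Day 8 and Day 15 (and sometimes Day 5) assessments that could be obtained are given up

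*Protocol article*

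**What the plan says.** Section 2.5 (Data collection and analysis) sets a mandatory rule: "Any participant experiencing persistent adverse effects will be withdrawn from the study and referred for appropriate follow-up care". Section 4 (Ethics and dissemination) returns to the subject for adverse effects in general, in softer terms: "Participants experiencing adverse effects will be offered appropriate support and may be withdrawn from the study if necessary". Both speak of leaving the study. Neither offers stopping stimulation while continuing assessment, and nothing else in the article provides for assessment after stimulation stops.

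The assessments at issue are these:

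- **Primary outcomes (section 2.4).** S-FCQ and FCI are "both administered before and immediately after stimulation sessions on Days 1 and 5", with Go/No-Go at the same times. The section adds: "These behavioral measures will provide insight into the acute and cumulative effects of tACS on craving regulation and impulse control".
- **Day 8.** Section 2.5 says the same three measures "will be administered pre- and post-stimulation on Days 1 and 5, and again on Day 8". The post-intervention fMRI is also on Day 8.
- **Day 15.** T-FCQ and YFAS 2.0 are repeated. The Figure 1 legend gives this visit the purpose of assessing sustained effects and adverse events.
- **Safety during the stimulation week (section 2.5).** "All adverse events or discomforts related to tACS will be monitored daily throughout the intervention phase".

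On analysis, section 2.5 declares intention-to-treat throughout. Missing values are to be filled by chained-equations multiple imputation (MICE) under missing at random, with sensitivity analyses under other imputation models.

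**The concern.** Stopping a treatment and leaving a trial are different events. Intention-to-treat works best when participants who stop treatment are still measured and are compared in the arm to which they were randomised. A rule that turns an adverse effect into departure from the study gives up those measurements by design, and no later analysis plan can bring them back.

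Two features make this more than a formality here. First, the reason for the loss is plausibly tied to the assigned arm. Section 2.3 gives 8 to 9 mA for the insula, 1.5 to 2 mA for the DLPFC and ACC, and a brief ramp with no sustained current in sham. Loss through adverse effects also puts strain on the missing-at-random assumption. Second, Day 15 is the scheduled visit for adverse events after the stimulation week. Under the rule, the participants who miss it are those whose adverse effects persisted.

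**Working it through.** **1. What is lost, by timing.** This concerns the four parallel FA+ arms and a withdrawal during the seven-day stimulation phase.

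| Withdrawal | Kept | Not taken, on the natural reading |
|---|---|---|
| After the Day 1 assessments, before Day 5 | Day 1 pre and post | Day 5, Day 8, Day 15 |
| After the Day 5 assessments | Every primary assessment listed in section 2.4 | Day 8, Day 15 |

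**2. What a different rule could recover.** A change from before to after stimulation on Day 5 does not exist once stimulation has stopped. A single Day 5 score can still be taken. Set against the Day 1 pre-stimulation score, it bears on the cumulative effect that section 2.4 mentions, although the article does not define that contrast. Day 8 craving, Go/No-Go and fMRI, and Day 15 trait measures and adverse events, can all be taken without stimulation.

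**3. Possible bias at Day 8.** The plan gives no figure to reproduce, and no rate of adverse-effect withdrawal.

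- From section 2.2.5: 35 per arm and f = 0.25. For two groups d = 2f = 0.5 SD.
- From section 2.5: time (pre/post) by group ANOVA for craving, and imputation under missing at random.
- Assumed: the contrast is Day 1 pre to Day 8, one active arm against sham; k = 1, 2 or 4 of 35 withdraw from the active arm; those who stay benefit by 0.5 SD at Day 8 and 0.25 SD on Day 1; the correlation r between any two measurements is 0.5 (range 0.3 to 0.7); imputation uses Day 1 pre, Day 1 post and arm.

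The time-by-group interaction is a comparison of change scores, so SE = √[(2/35) × 2(1 − r)]. This is 0.283, 0.239 and 0.185 SD for r = 0.3, 0.5 and 0.7.

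With p = k/35, the bias against full follow-up is p × (effect in those who stay − effect in those withdrawn). Positive values overstate benefit.

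| Withdrawn participants | Formula | k = 1 | k = 2 | k = 4 |
|---|---|---|---|---|
| Lose all benefit | 0.5p | +0.014 | +0.029 | +0.057 |
| Lose all, and had no Day 1 response | (0.5 − 0.25/3)p = 0.417p | +0.012 | +0.024 | +0.048 |
| Keep half | 0.25p | +0.007 | +0.014 | +0.029 |
| Do as well as those who stay | 0 | 0 | 0 | 0 |
| Do 0.25 SD better | −0.25p | −0.007 | −0.014 | −0.029 |

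In the second row the imputation slope on Day 1 post is r/(1 + r) = 1/3, so imputation takes back about one sixth of the bias. A simulation with four arms of 35, 5 imputations and 4000 replicates gave 0.0145, 0.0284 and 0.0567 for the first row, in agreement with the formula.

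Against the standard error at r = 0.5, the first row is 0.06, 0.12 and 0.24. For k = 4 the ratio runs from 0.057/0.283 = 0.20 to 0.057/0.185 = 0.31 over the range of r. For Go/No-Go by ANCOVA, SE = √[(2/35)(1 − 0.25)] = 0.207, and 0.057/0.207 = 0.28.

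**4. Balanced withdrawal.** Equal numbers leaving sham do not remove the first-row bias, because sham has no benefit to lose. The simulation gave +0.030 SD for 2 and 2, and +0.056 SD for 4 and 4. Between two active arms with the same effect, equal withdrawal would cancel.

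**5. Outer bound.** Suppose the whole 20% all-cause dropout allowance of section 2.2.5 were adverse-effect withdrawal in one arm, with none in sham. That is 7 of 35. A 0.5 SD departure from missing at random then gives 0.10 SD, and a 1 SD departure gives 0.20 SD. The latter is twice the assumed effect, so this is a limit and not an expectation.

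**The case against.** The strongest reply is that loss of data is inferred. The article nowhere says that assessments stop after withdrawal. Section 4 leaves withdrawal to judgement, and a condensed article may leave the distinction between stopping treatment and leaving the study to a full protocol that is not shown. This stands as a limit on how firmly the point can be put. It does not remove the point, because the rule in section 2.5 is stated and mandatory, and absence from later visits is its ordinary meaning.

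Ending participation can also be defended as a cautious safety choice, and the participant is still referred for care. That is fair, but stopping stimulation achieves the same protection.

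Several stronger readings are tempting, and the documents do not support them:

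- **That the rule contradicts intention-to-treat.** It does not. Imputation keeps every randomised participant in the analysis, and section 2.5 plans sensitivity analyses under other imputation models.
- **That the primary outcome is compromised in a way rewording would cure.** Section 2.4 places the primary assessments on Days 1 and 5. Day 1 values are kept, a pre/post-stimulation change on Day 5 cannot be had once stimulation stops, and Day 8 is not among the primary time points in that section.
- **That withdrawal will be unequal between arms, or the bias material.** No figure shows this, and section 2.3 cites evidence that higher-output tACS is tolerable. Equally, a reader might infer that the bias is certainly small. Without a withdrawal rate the documents cannot show that either.
- **That safety follow-up ends.** Section 4 promises adverse-event monitoring throughout the study and reporting of serious or unexpected effects to the ethics committees. What is lost is the scheduled Day 15 assessment for someone no longer in the study.

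**Conclusion.** The point holds as a minor weakness in a stated rule. Followed as written, section 2.5 gives up Day 8 and Day 15 data that could be obtained, and a Day 5 score if withdrawal is earlier. Imputation and sensitivity analyses can only stand in for these values.

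The size and sign of any bias are unknown. At 1 to 4 withdrawals of 35 in one arm, with full loss of a 0.5 SD benefit, the Day 8 contrast would be overstated by 0.014 to 0.057 SD. The upper figure is about a quarter of the standard error at r = 0.5. The bias is zero or reversed if those withdrawn do as well as or better than those who stay. All of this rests on assumed rates, effects and correlation, and on Day 8 as the post time point.

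The case for change rests less on bias than on keeping Day 8 craving, Go/No-Go and fMRI, Day 15 trait measures, and the Day 15 adverse-event assessment in the participants for whom it matters most.

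**What to change.** Replace the sentence in section 2.5 with, for example: *A participant with persistent adverse effects will stop stimulation and be referred for clinical care. Unless consent is withdrawn, the participant will attend the remaining scheduled assessments and be analysed in the randomised arm.* Align section 4 with it.

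The remaining assessments would be:

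- Day 5: one S-FCQ, FCI and Go/No-Go, without a pre/post pair, if no stimulation is given.
- Day 8: the same three measures, with fMRI only if clinically suitable.
- Day 15: T-FCQ, YFAS 2.0 and adverse events.

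When to stop stimulation stays with the investigators and ethics committees.

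The cost is protocol and consent wording. The visits are already scheduled, and section 4 says of ethics review: "Final approval will be obtained prior to initiating participant enrollment". The change can therefore be made before anyone is enrolled. The downside is that some participants attend visits after stopping stimulation, and the estimated effect may be slightly smaller.

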#### 2.2.5 Sample size and power considerations

The sample size was calculated based on prior studies investigating neuromodulation effects on craving-related behavior and oscillatory activity (Song et al., 2019, 2022; Althubaiti, 2022; Kim et al., 2023; Gairola et al., 2024; Arifin and Yaacob, 2025; Sánchez-Garrido Campos et al., 2025). Assuming a moderate effect size (Cohen’s f = 0.25), an alpha level of 0.05, and a desired power of 0.80, a minimum of 35 participants per group is required to detect statistically significant differences in the primary behavioral outcome.

To account for potential attrition and non-compliance, a 20% dropout rate was incorporated into the calculation, yielding a final target of 175 participants distributed across the five study groups. This includes 140 participants in the FA+ parallel groups and 35 in the FA- crossover group.

Given the multimodal nature of data collection, including repeated electroencephalography (EEG) and functional magnetic resonance imaging (fMRI) measurements, a sensitivity analysis was also conducted. This analysis confirmed that the study remains adequately powered to detect within-subject changes in neural and behavioral outcomes while maintaining sufficient statistical power for between-group comparisons.

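### The primary craving analysis compares change scores without adjusting for baseline craving, which is valid in the randomised FA+ arms but gives up precision that data already collected would supply

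*Protocol article*

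**What the plan says.** Section 2.4 names two primary outcomes, craving (S-FCQ and FCI) and inhibitory control (Go/No-Go). Section 2.5 then gives them different analyses within one paragraph:

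- **Craving:** change in S-FCQ and FCI "will be analyzed using repeated measures ANOVA, with time (pre/post) and group (stimulation target and sham) as factors". No baseline covariate is named. For the follow-up tests between groups, the plan adds that "comparisons will be corrected using the Bonferroni method", without giving their number.
- **Inhibitory control:** "Changes in Go/No-Go performance will be analyzed using ANCOVA, adjusting baseline reaction times and error rates".

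On data collection, section 2.5 says: "The S-FCQ, FCI, and Go/No-Go task will be administered pre- and post-stimulation on Days 1 and 5, and again on Day 8". A craving score taken before any stimulation is therefore available for every participant who starts treatment.

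Section 2.1 randomises FA+ participants to ACC, DLPFC, insula or sham stimulation. It says that the design serves comparisons of active with sham and also comparisons between cortical targets. The FA- group is a separate, non-randomised comparator with its own crossover, and this point does not concern it.

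**The concern.** When the time factor has two levels, the group-by-time term of a repeated-measures ANOVA is algebraically a one-way ANOVA of post minus pre. That fixes the slope on baseline at 1. ANCOVA estimates the slope from the data. In a randomised comparison both methods target the same treatment effect, but ANCOVA does so with a residual variance that is never larger (apart from one degree of freedom), and it corrects for chance imbalance in baseline craving more accurately.

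The protocol takes this route for Go/No-Go, and uses mixed models for EEG, but not for craving, and it gives no reason for the difference. At stake is the precision of one of the two primary outcomes in a four-arm comparison with a modest number per arm.

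**Working it through.** **The plan's own figure.** Section 2.2.5 states: "Assuming a moderate effect size (Cohen’s f = 0.25), an alpha level of 0.05, and a desired power of 0.80", and concludes that "a minimum of 35 participants per group is required to detect statistically significant differences in the primary behavioral outcome". A one-way ANOVA at f = 0.25, alpha 0.05 and power 0.80 needs 45 per group for four groups, or 40 for five; 35 per group gives 68% or 75%. A repeated-measures ANOVA for the between-group main effect (four groups, two measurements, assumed rho 0.5) gives 34, close to 35, but that is not the group-by-time test. The stated figure is thus not clearly reproduced. That is a separate matter, and nothing below depends on it.

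**Inputs**

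- From the protocol: f = 0.25; alpha 0.05; 35 per FA+ arm (140 over four arms, if equal).
- Assumed: rho, the correlation between the Day 1 pre-stimulation score and the analysed post score, over 0.3 to 0.8; equal pre and post variances SD²; two-sided contrasts; a Bonferroni family of either three (each active arm against sham) or six (all pairs).
- Effect size: if three equal active arms differ from sham by d SD, the SD of the four arm means is d√3/4. Setting this to 0.25 gives d = 4 × 0.25/√3 = 0.577.

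**Variances**

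- Change score: 2(1 − rho)SD².
- Baseline-adjusted: (1 − rho²)SD².
- Ratio: (1 − rho)(1 + rho)/[2(1 − rho)] = (1 + rho)/2.

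The direction does not depend on equal variances. With pre SD s0 and post SD s1, the change-score variance minus the adjusted variance is s0² + s1² − 2·rho·s0·s1 − s1²(1 − rho²) = (s0 − rho·s1)², which is never negative.

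**Power for one active arm against sham.** The noncentrality is d/√v × √(n/2), where v is the variance above in units of SD². The degrees of freedom are pooled over four arms: 136 for change, 135 for ANCOVA. At n = 35, √(n/2) = 4.183. The critical t is 2.42 for a family of three and 2.68 for six.

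Example at rho = 0.5. Change score: v = 1.00, noncentrality 0.577 × 4.183 = 2.415, power 50% (three) or 40% (six). ANCOVA: v = 0.75, noncentrality 2.415/√0.75 = 2.789, power 64% or 55%.

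| rho | variance ratio | power, family of 3: change → ANCOVA | power, family of 6: change → ANCOVA |
|---|---|---|---|
| 0.3 | 0.65 | 35% → 54% | 27% → 44% |
| 0.5 | 0.75 | 50% → 64% | 40% → 55% |
| 0.7 | 0.85 | 76% → 83% | 67% → 76% |
| 0.8 | 0.90 | 92% → 94% | 87% → 91% |

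A simulation of 4,000 trials at rho = 0.5 gave 39.7% for change scores with six pairs and 63.5% for ANCOVA with three contrasts, in agreement with the table.

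**If dropout leaves fewer.** Taking 20% off 35 leaves 28 per arm. With a family of three, power then goes from 28% to 44%, 40% to 53%, 64% to 72% and 84% to 88% over the same four values of rho.

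**The case against.** The strongest reply is that nothing here is invalid. A time-by-group ANOVA with Bonferroni correction is unbiased in randomised arms, different models for two outcomes are not a contradiction, and a condensed article may leave covariates to the analysis plan. The first two parts stand, so this is a matter of efficiency only. The third does not remove the point: the article does name the analysis for craving, and in the same paragraph it names baseline adjustment for Go/No-Go.

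A second reply is that the gain depends on a correlation that the protocol does not give. This stands too. Scores taken shortly before and after the same session could be highly correlated, and at rho = 0.8 the gain is only two to four percentage points.

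A reader might go further in three ways that the document does not support.

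- **Six pairwise tests waste error rate on active-against-active pairs.** Section 2.5 never says how many comparisons the Bonferroni correction covers. Section 2.1 declares comparison across targets as a purpose, so such pairs are not waste. Setting a change-score analysis with six pairs against ANCOVA with three contrasts (40% to 64% at rho 0.5) would mix the covariate's gain with that of a smaller, assumed family.
- **Day 8 should become the primary contrast.** Section 2.4 places the primary craving assessments on Days 1 and 5; section 2.5 and Figure 1 add Day 8. Moving the primary time point changes the question asked and is not needed in order to add a covariate.
- **Craving alone decides the trial.** Inhibitory control is also primary and is already baseline-adjusted.

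**Conclusion.** The point holds as one of efficiency: the planned craving analysis is a change-score comparison that leaves out a baseline covariate already collected. It is not biased, and its type I error is not in question.

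Adjustment reduces the variance by 35%, 25%, 15% and 10% at rho 0.3, 0.5, 0.7 and 0.8. In power this is worth about 14 to 19 percentage points at rho 0.3 to 0.5 and shrinks to about 2 to 4 at 0.8, across both families at 35 per arm. These sizes rest on the assumed rho, equal pre and post variances, f = 0.25 read as the same difference from sham in all three active arms, and a pre value taken before the first stimulation. The direction rests only on randomisation and on the slope on baseline differing from 1. The change is worth making, but the planned test would not be wrong without it.

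**What to change.** In section 2.5, replace the repeated-measures ANOVA for S-FCQ and FCI in the four FA+ arms with one of:

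- ANCOVA of the score at the sponsor's chosen primary time point, with group as factor and the Day 1 pre-stimulation score of the same scale as covariate; or
- a linear mixed model over all post-baseline assessments (Day 1 post, Day 5 pre and post, Day 8), with the same covariate, group, visit and group-by-visit, reading the treatment contrasts at the chosen time point.

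Keep the sponsor's primary time point and comparison family, and state both. Include the baseline score in the imputation model, so that it matches the analysis model.

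Separately and optionally, the sponsor may limit the confirmatory family to three active-against-sham contrasts, for example with Dunnett's method. This gains power against sham, but makes the comparisons across targets secondary, so it is a trade-off for the sponsor to decide.

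The covariate costs a change of wording and one degree of freedom, with no new data, visits or participants. According to section 4, ethics approval and registration are to come before enrolment, so the wording can be settled before any data exist.
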